### Aim 3: Acceptability, Feasibility, and Preliminary Efficacy

#### Trial Design

The pilot trial will be a single-blind parallel superiority trial assessing NOLA GEM (treatment arm) against GEMA alone (control arm) for a period of 21 days, allocated at a 1:1 ratio. In contrast to aim 1, the NOLA GEM app is capable of delivering SMS text message–linked daily diaries and recording GPS coordinates without recourse to third-party software. The GEMA-alone control was chosen to control for any intervention effects of recording daily mood, experiences, and other psychosocial variables as some research has demonstrated improvements in outcomes such as PTSD, depressive symptoms, and emotional awareness in participants recording their experiences using EMA methods [112-115] (aim-2 interviewees, unprompted, disclosed similar enhancements in self-awareness during their experience as aim-1 participants). This design establishes a high-resolution comparator to NOLA GEM, capturing GEMA data across both trial arms while potentially isolating the effects of JITAI-based momentary provision of LIFT content as a hypothesized mechanism of action.

#### Screening

The aim-3 inclusion criteria are equivalent to those of aims 1 and 2, although both HIV outpatient clinic–based as well as community-based recruitment strategies will be used, inviting people living with HIV across the New Orleans metropolitan area to learn about the study through flyers and screening in real time via a QR code. Once the code is scanned, users will be brought to a Qualtrics survey that will ask basic demographic questions to facilitate quota sampling, history of living with HIV, current ART medications, and past violence exposure, which will be assessed via the *Adverse Childhood Experiences Questionnaire* and US Department of Veterans Affairs National Center for PTSD *Life Events Checklist for DSM-5* [116].

An option to screen by phone, with a research assistant manually inputting each potential participant’s screener responses, will also be available. Once individuals are determined to meet the eligibility criteria, they will be called to set up an intake appointment.

#### Sample Size Considerations

The target sample size is approximately 100, which will accommodate an anticipated ≥10% attrition rate based on previous experience enrolling local violence-affected in-care people living with HIV, for an optimal analytic sample of 60 (30 per arm).

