**Methods:**

The development of NOLA GEM entailed identifying real-time tailoring variables via a geographic ecological momentary assessment (GEMA) study (n=49; aim 1) and place-based and user-centered tailoring, responsive to the unique cultural contexts of HIV survivorship in New Orleans, via formative interviews (n=12; aim 2). The iOS- and Android-enabled NOLA GEM app leverages twice-daily GEMA prompts to offer just-in-time, in-app recommendations for effective coping skills practice and app-delivered *Living in the Face of Trauma* session content. For aim 3, the pilot trial will enroll an analytic sample of 60 New Orleans people living with HIV individually randomized to parallel NOLA GEM (intervention) or GEMA-alone (control) arms at a 1:1 allocation for a 21-day period. Acceptability and feasibility will be assessed via enrollment, attrition, active daily use through paradata metrics, and prevalidated usability measures. At the postassessment time point, primary end points will be assessed via a range of well-validated, domain-specific scales. Care engagement and viral suppression will be assessed via past missed appointments and self-reported viral load at 30 and 90 days, respectively, and through well-demonstrated adherence self-efficacy measures.

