### Limitations

As a small-scale pilot trial, aim 3 is subject to a number of inherent limitations. First, and by design [142], it is underpowered to examine efficacy in a formal hypothesis-driven manner. Mediation analyses of proximal outcomes will necessarily be exploratory in nature and inform the causal pathway hypotheses for the planned RCT. Although the selection of control conditions for mHealth trials remains an area of active investigation and debate [143], a passive GEMA-alone control may inflate preliminary estimates of NOLA GEM (incorporating GEMA+LIFT coping skills) efficacy on primary outcomes, an issue that is potentially exacerbated by the small sample size [144]. Adaptations of complex, sequential, and multicomponent group interventions risk dismantling key mechanisms of action that undergird effectiveness in their original contexts [33,34,101]. Adaptation to mHealth across HIV science remains a highly active but often methodologically impromptu area [145]. Pragmatic considerations required us to deprecate certain components of LIFT as originally manualized [33] and demonstrated to reduce traumatic stress [34,36]. Group cohesion and dedicated in-person facilitation of the group member disclosure and support processes define the LIFT intervention trajectory, which is sequenced across 15 sessions [33]. We abstracted the CTSC-based strategies built into NOLA GEM from their original, in-person, session-by-session framework to activate the “just-in-time” aspect of a JITAI adaptation while mitigating ethical concerns that, if faced with an acute stressor, a NOLA GEM user would be denied the best-suited coping support if they had not yet reached the appropriate session had a strictly linear intervention model been retained. Similarly, although a peer-to-peer support forum or social media–style feature [146,147] in which users could interact pseudonymously was briefly considered, lacking active human (vs algorithmic) content moderation, such a space could become consumed with off-topic, inane, or even outrage-inducing user-generated content and external media [86,148]. In addition, by recruiting people living with HIV who were either violence-affected individually or lived in a high-violence neighborhood, a degree of heterogeneity in needs was introduced into the aim-1 and aim-2 samples, which may have swayed the formative insights—and, by extension, intervention design—derived from the *New Orleans Alcohol Use in HIV* study subsamples. Although violence exposure at the within-person and neighborhood levels is associated with distinct sequelae among people living with HIV, it is our intention that the multitude of possible NOLA GEM user journeys can offer the necessary support to a wide range of personal violence histories. By nature, an acceptability and feasibility trial will provide insights on many of these concerns, whereas merged paradata and GEMA data will permit high-resolution analyses of users’ engagement with and navigation of NOLA GEM [149].

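### The only attrition figure given (at least 10%) does not lead from a target of about 100 to an analytic sample of 60: at 10% it gives about 90, and reaching 60 takes about 40% loss

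*Protocol article*

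**What the plan says.** The Sample Size Considerations section for aim 3 sets out the whole calculation in one sentence. It opens with "The target sample size is approximately 100, which will accommodate an anticipated ≥10% attrition rate", attributes that rate to the team's earlier experience with a similar local population, and ends "for an optimal analytic sample of 60 (30 per arm". The Trial Design section confirms equal allocation to the two arms.

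The abstract's Methods paragraph gives only the smaller number: "the pilot trial will enroll an analytic sample of 60 New Orleans people living with HIV". It mentions neither 100 nor any attrition rate.

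Three other places bear on the point:

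- The aim-3 Participants and Procedures section has eligible people randomized and then scheduled for a baseline appointment, where consent is obtained.
- The abstract and the Acceptability, Feasibility, and Usability section make attrition something the pilot will record and report.
- The Limitations section says of the trial that "it is underpowered to examine efficacy in a formal hypothesis-driven manner".

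**The concern.** A sample-size statement of this kind has three parts: how many to recruit, what share will be lost, and how many remain for analysis. Any two fix the third. Here all three are given, and the stated rate does not link the other two. The gap is 30 people, half the stated analytic sample, so it is not a matter of rounding.

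This matters mainly because attrition is one of the pilot's own acceptability and feasibility measures. As written, the implied expectation lies anywhere between 10% and 40% loss. If 60 of 100 people remain, that is on plan under one reading and well short of it under the other. The abstract adds to the uncertainty by using one number for people enrolled and people analysed, so a reader cannot tell how many people the trial intends to randomize.

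**Working it through.** **Inputs**

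- Target sample size N: about 100 (Sample Size Considerations).
- Attrition d: at least 10%, the only rate given (same section).
- Analytic sample: 60, or 30 per arm (same section; 60 also in the abstract).
- Allocation: 1:1 (Trial Design).
- Significance level, power, effect size and standard deviation: none stated. The attrition arithmetic is therefore the only calculation to check.

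**Attempt to reproduce the plan's figure of 60**

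Analysed number = N × (1 − d) = 100 × (1 − 0.10) = 90, or 45 per arm. The plan states 60, or 30 per arm. The difference is 90 − 60 = 30.

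**Working back from 60**

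Required target = 60 / (1 − d) = 60 / 0.90 = 66.7, rounded up to 67. The common shortcut 60 × (1 + 0.10) gives 66. Neither is near 100.

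**Attrition implied by the pair 100 and 60**

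d = 1 − 60/100 = 0.40. Relative to the stated rate this is 0.40 / 0.10 = 4 times.

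**Variants that might close the gap**

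| Variant | Calculation | Result |
|---|---|---|
| Target read as 95 | 95 × 0.90 | 85.5 analysed |
| Target read as 105 | 105 × 0.90 | 94.5 analysed |
| 10% lost at each of two stages | 100 × 0.90 × 0.90 | 81 analysed |
| 20% attrition | 100 × 0.80 | 80 analysed |
| 30% attrition | 100 × 0.70 | 70 analysed |
| 40% attrition | 100 × 0.60 | 60 analysed |

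Looseness in the word *approximately* does not help: with a target of 95 to 105, the loss needed to reach 60 runs from 1 − 60/95 = 37% to 1 − 60/105 = 43%. The article states no second source of loss, such as a no-show rate before consent or a minimum diary-completion rule, that would take 90 down to 60.

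**The case against.** The strongest reply is that the rate is a floor. A 40% loss is at least 10%, so all three numbers can be true together. That is correct. A reader might infer that the sentence contradicts itself outright, and the text does not support that. What survives is narrower: the rate is offered as an anticipated value drawn from experience and as the reason for the target, and a bound that fits any result from 90 downward justifies neither 100 nor 60.

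A second reply is that the 100 need not be people enrolled. The sentence speaks of a target sample size, and randomization comes before the baseline visit and consent, so people who never attend or never consent could be among the 100. This is possible, but the article does not say so and gives no rate for such losses. It shows that the denominator is undefined; it does not rescue the sum.

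A third reply is that little depends on the sentence. The pilot is declared underpowered for efficacy by design, and no power calculation rests on 60. If only 10% were lost, the trial would have more data than the 60 it calls optimal. This holds, and it limits the seriousness of the point. The abstract's choice of verb is likewise loose wording in a condensed text, since it does call the 60 an analytic sample.

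Two further inferences are tempting and should not be drawn. One is that the pilot's attrition rate will set the size of the later trial: the article says that the pilot should support the feasibility of, and a funding application for, a full trial, but not that this rate will size it. The other is that recruitment will stop once 60 people have completed, leaving a completers-only analysis: no section describes such a rule, and the only recruitment target stated is about 100.

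**Conclusion.** The concern holds in a limited form. On the one rate given, a target of about 100 leads to about 90 analysed (45 per arm), not 60 (30 per arm); 60 analysed would need a target of 67; and the pair 100 and 60 implies about 40% loss, or 37% to 43% if the target is read as 95 to 105. The statement is not logically impossible, because the rate is a lower bound, but it fails as a planning statement.

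The conclusion assumes that the three figures describe the same group of people and that attrition means loss from the target number to the analysed number. If the 100 includes people lost before consent, the missing figure is that earlier loss, and the text still has to state it.

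This should be corrected because it leaves the expected value of a declared outcome undefined. It does not undermine the design, and no hypothesis test or power claim rests on it.

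**What to change.** Keep the target of about 100 and make these changes to the text:

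1. In Sample Size Considerations, say whether the 100 counts people screened, randomized or consented. Because randomization precedes consent, these can be different numbers.
2. Replace the open-ended rate with one coherent pair. Either expect about 90 analysed (45 per arm) at 10% attrition, with 60 (30 per arm) as the minimum at 40%; or plan for 60 analysed with a 40% loss stated openly. Under the first option, 60 should no longer be called optimal.
3. Use the chosen rate as the expected value for the attrition outcome named in the abstract and in Acceptability, Feasibility, and Usability.
4. In the abstract, replace the verb *enroll* so that the number recruited and the number analysed are distinct and agree with the body.

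The cost is wording only. The recruitment target does not change and no further participants are needed. The sponsor does have to commit to an expected attrition rate, and under the second option that rate is less favourable than the article now suggests. Cutting the target to 67 would also make the sum work, but it would lower the stated recruitment target by a third (33 of 100), which is a change of plan and not a clarification.

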#### Study Settings

Participants will be recruited using flyers from several clinics and community locations in New Orleans that offer services to people living with HIV. Many of the community sites provide linkage to care by guiding people through insurance eligibility, appointments, and medication access. Two of these community sites were founded to provide services specifically to Black and African American women living with HIV. The clinic sites are federally qualified health centers that provide a range of care; however, we are working specifically with their HIV prevention and care teams.

By and large, aim 3 will comprise a digital trial subsequent to NOLA GEM onboarding. Screeners will be completed either on the participants’ phones or by calling research staff. Once participants are screened, intake appointments will take place either over Zoom or at private clinical facilities within the Tulane University School of Public Health and Tropical Medicine. All further aspects of the study will take place on the NOLA GEM app or over the phone.

#### Participants and Procedures

With eligibility determined, participants will be randomized, and a baseline appointment will be scheduled. Quota sampling will ensure a ≥50% female, 50% aged >40 years and 50% aged <40 years, and ≥75% Black sample, reflecting the unique drivers and PTSD symptom constellations endured by women and Black Americans while also reflecting New Orleans people living with HIV demographics.

At baseline, informed consent will be obtained, and an in-person or Zoom assessment will be administered by the research staff. The NOLA GEM app (through which participants can be assigned to either treatment or control user types via an integrated back end) will be installed on participants’ smartphones from the Crowdbotics-hosted Apple App Store or Google Play Store, and a detailed onboarding will be conducted by research staff to ensure uniform comprehension of the app’s features, the nature of GEMA, and the wording of daily diary items. Although participants will be instructed on the expectations, functional affordances, and user expectations specific to their trial arm, they will be blinded to their explicit treatment versus control assignment.

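### Participants are stated to be randomized before consent and before the baseline assessment, which creates avoidable post-randomization exclusions

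*Protocol article*

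**What the plan says.** All references are to the aim-3 part of the protocol article.

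- **Screening.** Eligibility is judged from an online survey reached by QR code, or from the same screener taken by phone. Then: "Once individuals are determined to meet the eligibility criteria, they will be called to set up an intake appointment".
- **Study Settings.** The same order appears: "Once participants are screened, intake appointments will take place either over Zoom or at private clinical facilities".
- **Participants and Procedures.** Allocation is placed between the screener and the visit: "With eligibility determined, participants will be randomized, and a baseline appointment will be scheduled". The next paragraph says what happens at the visit: "At baseline, informed consent will be obtained, and an in-person or Zoom assessment will be administered by the research staff". App installation and onboarding come after that, with instruction specific to the arm. On the app, "participants can be assigned to either treatment or control user types via an integrated back end". On blinding, the section says of participants that "they will be blinded to their explicit treatment versus control assignment".
- **Trial Design.** The trial is called single-blind. No section says that research staff are blinded.
- **Analytic Approach.** The mixed models for day-level outcomes adjust for baseline values. Under Domain–General Stress, the 30-day stressor checklist is read relative to baseline burden.
- **Acceptability, Feasibility, and Usability.** Screening and enrollment rates are feasibility measures, and attrition is recorded as well.

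**The concern.** Randomization makes the arms comparable as sets of randomized people. If allocation rests on a screener alone, some of those people will not attend and some will decline consent. They provide no consented trial data, so the analysed set is a subset of the randomized set before any follow-up has begun. Randomizing after consent and baseline avoids this.

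Two further things are at stake. First, the baseline assessment is a covariate and, for the stressor checklist, a reference point. Here it is administered by staff after an allocation exists. Second, the pilot is meant to supply enrolment and attrition rates for a full-scale trial. A person randomized but never consented fits neither category cleanly, so those rates depend on a counting choice that the stated order makes necessary.

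**Working it through.** **1. The order of events.** The plan gives no figure for this point, so the check is a reading of the sections side by side.

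| Step | Event | Section |
|---|---|---|
| 1 | Eligibility from QR-code or phone screener | Screening |
| 2 | Randomization; baseline appointment scheduled | Participants and Procedures |
| 3 | Appointment takes place (Zoom or clinic room) | Study Settings |
| 4 | Informed consent | Participants and Procedures |
| 5 | Baseline assessment by research staff | Participants and Procedures |
| 6 | App installation and arm-specific onboarding | Participants and Procedures |

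Screening and Study Settings call the visit an intake appointment, and Participants and Procedures calls it a baseline appointment. I take them to be the same visit. The conclusion does not depend on this, because consent is placed at baseline and randomization is placed before it. No section puts trial consent or baseline measurement before step 2.

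**2. When the order would bias the comparison.** Let u₁ and u₀ be the proportions of each arm lost between steps 2 and 4. Let k₁ and k₀ be the gaps in mean outcome between those kept and those lost. Within an arm, the mean of those kept differs from the mean of all randomized by u × k. With no treatment effect, the expected difference between the kept groups is therefore

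bias = u₁k₁ − u₀k₀.

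If nobody who influences attendance, consent or assessment knows the arm, then u₁ = u₀ and k₁ = k₀ in expectation, and the bias is 0. A non-zero value needs arm knowledge to enter somewhere in steps 2 to 5. The documents give none of u₁, u₀, k₁ or k₀, so no value can be computed.

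**3. What loss unrelated to arm does to the feasibility rates.** Assume, for illustration only, that 100 people are randomized, that a proportion u is lost before consent equally in both arms, and that 10% of those who consent are lost later. The 10% is the lower bound under Sample Size Considerations. The values of u are assumptions.

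Consented = 100 × (1 − u). Analysed = consented × 0.9. Attrition is 10% if pre-consent losses count as non-enrolment, and (100 − analysed)/100 if they count as attrition.

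| u (assumed) | Never consented | Consented | Analysed | Attrition, counted as non-enrolment | Attrition, counted as attrition |
|---|---|---|---|---|---|
| 5% | 5 | 95 | 85.5 | 10% | 14.5% |
| 10% | 10 | 90 | 81 | 10% | 19% |
| 20% | 20 | 80 | 72 | 10% | 28% |
| 30% | 30 | 70 | 63 | 10% | 37% |

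The same trial can thus report quite different attrition with no bias present. If randomization follows consent and baseline, the two columns coincide.

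**The case against.** **Participants do not know their arm.** They are blinded to explicit assignment, and arm-specific instruction comes only at onboarding, after consent and assessment. A reader might infer that people will stay away or refuse because of the arm they drew. The documents do not support that, and this part of the objection stands in full.

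**Silence on concealment is not a fault here.** A condensed article commonly leaves the holder of the allocation list, and the time staff see it, to the full protocol. A reader might infer that schedulers and assessors can see the allocation, but no section says so. What remains is narrower: the stated order has staff obtain consent and assess baseline after allocation, and the article does not describe them as blinded.

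**Baseline answers precede exposure.** In the order given, participants answer before they see any app content. Adjusting for these values is not adjusting for something the treatment has changed. That stands; the only remaining route is through the staff who administer the assessment.

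**Allocation may really happen in the app.** If setting the user type in the back end is the true moment of allocation, the defect is a misordered sentence. The text describes a mechanism and gives no time for it, and under this reading the sentence still needs correcting.

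**The sample-size gap is not evidence of pre-consent loss.** Ten percent attrition needs 60/0.9 = 66.7, so 67 people, against a target of about 100. A reader might infer that the other 100 − 67 = 33 are expected losses between randomization and consent. The article does not say that 100 is the number randomized, it gives attrition only as a lower bound, and it states no such split. The gap is a separate question.

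**No counting rule is stated.** A reader might infer that pre-consent no-shows will be counted as attrition. No section says so, and they could as naturally be losses between screening and enrolment. The point is only that the order leaves this open.

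**Conclusion.** The order is stated plainly and no other section contradicts it: randomization comes before consent and before the baseline assessment. Two consequences follow directly. People who miss the visit or decline consent become post-randomization exclusions, and baseline values are collected after allocation by staff who are not stated to be blinded.

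Bias in the treatment comparison is conditional. It arises only if staff know the arm and that knowledge affects scheduling, consent or baseline assessment. Its size cannot be stated, because the documents give neither a no-show or refusal rate nor any outcome difference between those lost and kept. It would be wrong to conclude that the comparison is broken.

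The ambiguity in the feasibility rates does not need that condition. It matters for this pilot even though the Limitations section says the trial is underpowered for efficacy by design, because these rates inform the planned larger trial. The attrition figures in the table rest on assumed loss rates and show only how far the counting choice can move the result.

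This is a cheap improvement.

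**What to change.** Amend the first paragraphs of Participants and Procedures so that the order is: screen, appointment, informed consent, completed baseline assessment, then release of the allocation when the app user type is set at the same appointment. Define the randomized set from that point, and count earlier losses as losses between screening and enrolment. If this is already the practice, correct the sentence to say so.

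The Results section says that recruitment began in July 2023, so some people may have been randomized in the published order. For them, report the number randomized but not consented, by arm.

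The app is already installed at this visit, so the documents suggest that no visit need be added. The cost is a small change to the appointment workflow, because the allocation has to be released during the visit rather than before it.
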